### Data analysis

All data will be entered into a SPSS database (version 16.0 for Windows®; SPSS Inc., Chicago, IL, USA). Data analysis will be described following our two study aims.

#### Effectiveness of the multifaceted approach

To analyze the effectiveness of the multifaceted approach on patient-centeredness, patients’ QoL and levels of distress, the difference in baseline and after-measurement scores will be analyzed with adjustment for clustering of patients within clinics. Multilevel linear regression analyses will therefore be performed in which the intervention (multifaceted approach vs. usual care) will act as the independent variable. The Patient-centredness Questionnaire – Infertility total and subscale scores, the FertiQoL total scores and the SCREENIVF scores will be used as dependent variables. Differences at baseline will be corrected for by taking baseline scores as a covariate in the final multilevel models.

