### Study design

In a cluster-randomized trial, the effects of a multifaceted approach on the level of patient-centered fertility care, patients’ QoL and the level of distress will be identified. To include a representative patient group for baseline measurement, clinics will be asked to extract the address files of all patients who underwent medically assisted reproduction in their clinics during the past 3 months (2011) from their diagnosis treatment combination coding system. Per clinic, 25 to 75 patients will be randomly selected depending on the clinic’s size. Participation is voluntary and anonymous. The couples will receive a letter with an invitation to participate. If they are willing, they complete an online questionnaire set, accessible by a personal code. Two weeks after the initial mailing, all patients will receive a reminder. Another 3 weeks later, nonresponders will receive a reminder with their personal codes and the additional option to complete a paper version of the questionnaire
[29].

Following baseline measurement, all 32 participating clinics will be randomly assigned to usual care (16 clinics) or to the multifaceted approach (16 clinics) with stratification for clinic size (large/medium/small) and IVF facilities (full licensed/intermediate/no IVF facilities).

After 1 year of intervention exposure, all clinics again extract the address files of all patients who underwent medically assisted reproduction in the last 3 months for the after measurement. The same questionnaire set will be used, which again have to be completed by both the women and the partners separately. Figure
1 illustrates the study design schematically.

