#### Determinants of change in patient-centeredness, patients’ QoL and distress levels

First, all independent variables concerning baseline patient and clinic characteristics will be checked for colinearity. These variables include all patient and clinic background characteristics, as well as the four variables concerning hospital culture, and the team characteristics collected during EOV.

If a correlation coefficient >0.6 is found between two variables, preference will be given to the variable theoretically closest to actual outpatient performance. Subsequently, all independent variables will be tested in a univariate analysis with the dependent variables concerning the differences between patient-centeredness, patients’ QoL and levels of distress in baseline and after measurement. The variables tend to be associated and show enough interclinic variation will be included in three multilevel linear regression models to explain differences in an increase in patient-centeredness, an increase in patients’ QoL and a decrease in levels of distress, respectively. To assess which part of the variation can be explained by the determinants, the explained variance (*R*^2^) per model will be calculated. Significance for all analyses will be set at *P* <0.05.

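### The two surveys are separate cross-sections with no linkage described, so the individual before-after change and own-baseline covariate in the analysis cannot be computed for most women; change exists only at clinic level

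*Protocol article*

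**What the plan says.** **Sampling (Study design).** At baseline each clinic lists the patients it treated in a 3-month period in 2011, and 25 to 75 per clinic are drawn at random. For the second survey, held once the intervention has run for a year, the article says: "all clinics again extract the address files of all patients who underwent medically assisted reproduction in the last 3 months". It also states: "Participation is voluntary and anonymous". A personal code gives access to the online questionnaire, and no use of that code across surveys is described.

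**Effectiveness analysis.** The article says that "the difference in baseline and after-measurement scores will be analyzed with adjustment for clustering of patients within clinics". It names the questionnaire scores as dependent variables and the intervention as independent variable in a multilevel linear model, and adds: "Differences at baseline will be corrected for by taking baseline scores as a covariate in the final multilevel models".

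**Determinants analysis.** All candidate variables, patient characteristics as well as clinic characteristics, culture and team variables, are tested "with the dependent variables concerning the differences between patient-centeredness", quality of life and distress at the two measurements. The stated aims cover determinants at both patient and clinic level.

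**The concern.** The sampling describes repeated cross-sections of clinics, whereas the analysis is worded as if a cohort of patients were followed. The two do not fit. A woman first sampled at the second survey has an after score but no before score, so she has neither a difference to analyse nor a baseline value to adjust for. Nowhere does the article say that the difference or the baseline score is a clinic mean.

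Two things are at stake. For effectiveness, which covers all three outcomes, the analyst must decide later what baseline and difference mean, and the possible choices are not equivalent. For the second aim, patient-level determinants of change have no outcome to be related to.

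**Working it through.** **1. Can the same women be in both surveys by design?** The baseline period ends before randomization. The second period is the last 3 months before an extraction made after at least 12 months of exposure, so it begins at least 12 − 3 = 9 months after exposure starts. The two treatment periods do not overlap, and no step re-contacts baseline respondents.

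**2. Does the sample size imply a cohort?** The article's invitation figure reproduces: 1,023 / 0.70 = 1,461.4, rounded up to 1,462 at each measurement. Non-response is allowed for once per survey. If the same couples had to answer twice at 70% each time, 1,462 × 0.70 × 0.70 = 716 would give both scores, well short of 1,023. The figure fits two separate surveys. (Whether 1,023 follows from its own inputs is a separate matter, and nothing here depends on it.)

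**3. How many women could have both scores by chance?** The article gives no figure, so this is an assumed range:
- share of after-measurement women who were also eligible at baseline: 10% to 50%;
- share of eligible women sampled at baseline: 30% to 60%;
- response: 70% (Sample size calculation).

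Low end: 0.10 × 0.30 × 0.70 = 0.021. High end: 0.50 × 0.60 × 0.70 = 0.21. So about 2% to 21% of after-measurement respondents would have their own baseline score, provided the surveys were linked. They would be long-treated, non-pregnant women, because pregnant couples are excluded, and so not a representative subset.

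**4. What can be estimated?**

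| Quantity | Available from two unlinked surveys? |
|---|---|
| Individual change score | No |
| Own baseline score as covariate | No |
| Clinic mean at baseline as covariate | Yes |
| Change in clinic means, related to clinic characteristics | Yes |
| Patient characteristic related to individual change | No |
| Patient characteristic related to the after score, and its interaction with arm | Yes |

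**5. Caution if both surveys are stacked.** The article does not describe this model, but it is one way an analyst might proceed. Inputs: ICC ρ = 0.13 (Sample size calculation); 32 clinics; m = 1,023 / 32 ≈ 32 respondents per clinic per survey; r = correlation of a clinic's true level between surveys, which is **not in the document** and is varied. Total variance is set to 1.

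- True variance of the change contrast is proportional to ρ(1 − r) + (1 − ρ)/m.
- A model with a clinic intercept only reports approximately [(1 − ρ) + ρ(1 − r)·m/(2m − 1)]/m.
- Example, r = 0.9: true 0.0130 + 0.0272 = 0.0402; reported (0.87 + 0.0066)/32 = 0.0274; SE ratio √(0.0402/0.0274) = 1.21; actual error 2[1 − Φ(1.96/1.21)] = 0.106.

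| r (assumed) | True SE / reported SE | Actual rate of a nominal 5% test |
|---|---|---|
| 1.0 | 1.00 | 5% |
| 0.9 | 1.21 | 11% |
| 0.8 | 1.39 | 16% |
| 0.7 | 1.54 | 20% |
| 0.5 | 1.81 | 28% |

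Simulation under no effect (20,000 runs per setting) agrees with these rates to within half a percentage point. Adjusting for the clinic's baseline mean, with clinic-based degrees of freedom, stayed close to 5% throughout.

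**The case against.** The best defence is that the Effectiveness section already comes close to a sound model. It makes the scores themselves the dependent variables, with intervention as predictor, baseline scores as covariate and patients nested in clinics. If baseline scores means the clinic's mean baseline score, that is the model recommended below, and only one clause is missing. This stands in part: the effectiveness analysis can be recovered without new data. But no sentence says clinic mean, the sentence on the difference points the other way, and the clinic-mean reading cannot rescue patient-level determinants of change.

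It can also be said that some women may answer twice. Treatment may last years, earlier participants are not excluded from the second extraction, and personal codes and reminders to nonresponders suggest that replies are traceable within a survey. That also stands, so it would be wrong to say that no woman could have two scores. The exception is small, however, and usable only with a linkage that the article does not describe.

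Third, aim 2 is only partly affected. The determinants analysis asks for variation between clinics, and culture, team and other clinic variables can be related to clinic-level change. That is correct.

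Finally, exact degrees of freedom and random-effect structure are usually left to a full protocol or analysis plan. Their absence is not the point here. The point is that the stated design and the stated analysis disagree.

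**Conclusion.** The point holds as a conflict between the sampling and the analysis. It follows from the text alone and needs no assumed figure. Individual change and own-baseline adjustment are not available for most women, and patient-level determinants of change cannot be estimated as stated. Clinic-level analyses remain open.

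A reader might infer three stronger things that the document does not support:
- **That the trial's test has an error rate of 11% to 28%.** Those rates belong to a stacked model with a clinic intercept only, which the article does not describe, and they rest on assumed between-survey correlations of 0.9 to 0.5. They are a caution about one possible workaround.
- **That using a difference costs precision compared with baseline adjustment.** The plan already includes baseline as a covariate. In a linear model, regressing change on arm and baseline gives the same arm estimate and standard error as regressing the after score on arm and baseline.
- **That the main analysis has no usable data.** After-measurement scores and clinic baseline means exist for every clinic that responds at both surveys.

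The 2% to 21% overlap is illustrative and rests on the assumed inputs shown.

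**What to change.** **Effectiveness section.** Replace the sentences on the difference and on baseline correction. State the primary analysis as the woman's individual after-measurement score on arm, with the clinic's mean baseline score as a clinic-level covariate, a random clinic intercept, and inference based on the number of clinics (32).

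**Determinants section.** Test patient-level determinants on the after-measurement score, as a main effect and as an interaction with arm. Restrict the word change to clinic-level means and relate it only to clinic-level characteristics. Reword the patient-level part of the second aim to match.

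**If the surveys are stacked instead.** Use arm by period with random clinic and random clinic-by-period effects.

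**Repeat respondents.** If the personal codes can be linked within the promise of anonymity, flag women sampled in both surveys; otherwise say that they cannot be identified.

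**Cost.** Wording only, with no new data and one clinic-level degree of freedom. Claims about individual change are given up. According to Trial status the intervention had only just begun, so at that stage the wording could be settled before any after-measurement data existed.

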#### Determinants of change in patient-centeredness, patients’ QoL and distress levels

First, all independent variables concerning baseline patient and clinic characteristics will be checked for colinearity. These variables include all patient and clinic background characteristics, as well as the four variables concerning hospital culture, and the team characteristics collected during EOV.

If a correlation coefficient >0.6 is found between two variables, preference will be given to the variable theoretically closest to actual outpatient performance. Subsequently, all independent variables will be tested in a univariate analysis with the dependent variables concerning the differences between patient-centeredness, patients’ QoL and levels of distress in baseline and after measurement. The variables tend to be associated and show enough interclinic variation will be included in three multilevel linear regression models to explain differences in an increase in patient-centeredness, an increase in patients’ QoL and a decrease in levels of distress, respectively. To assess which part of the variation can be explained by the determinants, the explained variance (*R*^2^) per model will be calculated. Significance for all analyses will be set at *P* <0.05.

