[13-16]. Moreover, because of the high physical and emotional burden, about 23% of couples end treatment prematurely
[17]. Given these high percentage of patients deciding to terminate treatment early, frequently as a result of high psychological and psychical impact, every clinic should optimize its care towards more patient-centered care
[13,14].

In Dutch fertility care, van Empel and colleagues showed that several parts of patient-centeredness could be improved
[18]. How such improvement initiatives can be undertaken most successfully is still unknown. Moreover, there are potential barriers impeding improvement initiatives. For instance, professionals in fertility care underestimate the importance of patient-centeredness and have difficulties in estimating their performance correctly
[19]. Another barrier may be the organizational culture of a hospital. For instance, patients visiting hospitals that support teamwork are more satisfied with their care than patients visiting hospitals with other culture types (for example, hierarchical culture)
[20-23]. Moreover, providing patient-centered care is often thought to be expensive and time consuming
[24,25].

Obviously, steps need to be taken to achieve a behavioral change in professionals towards providing more patient-centered care. Because no magic bullets exist for changing healthcare providers’ behavior
[26], multiple interventions based on known barriers could accomplish this behavioral change and improve patient-centered care.

We designed a study to evaluate the effects of a quality improvement strategy consisting of three different elements; that is, a multifaceted approach. We hypothesize that providing clinicians with this multifaceted approach will improve the level of patient-centeredness and thus healthcare quality. If so, this is essential in improving patients’ QoL, reducing levels of distress and percentages of patients discontinuing treatment, and eventually reducing healthcare costs.

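### The determinants models do not name randomised arm, and they mix variables from all 32 clinics with outreach-visit variables that can exist only in the 16 intervention clinics

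*Protocol article*

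**What the plan says.** All references are to the Protocol article.

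- **Candidate variables.** Under Data analysis, the subsection on determinants of change begins with a collinearity check: "all independent variables concerning baseline patient and clinic characteristics will be checked for colinearity". The list is then spelled out: "These variables include all patient and clinic background characteristics, as well as the four variables concerning hospital culture", "and the team characteristics collected during EOV".
- **Procedure.** Where two variables correlate above 0.6, one is preferred. Each variable is tested on its own against the change in each outcome. Those that look associated and vary enough between clinics go into "three multilevel linear regression models to explain differences in an increase in patient-centeredness" and in the other two outcomes. Explained variance is reported, and significance is set at P < 0.05.
- **Where arm appears.** Arm is named in the preceding subsection, for the effectiveness model: "the intervention (multifaceted approach vs. usual care) will act as the independent variable". The determinants subsection does not mention it.
- **Where the variables come from.** Under Clinic characteristics, the culture and general clinic questions go to professionals at all 32 hospitals. The team scores are recorded by the researcher at the EOV, which The intervention section describes as one of the three elements of the approach.
- **Aim.** The closing paragraph of the Background lists determinants of an increase or decrease in the outcomes as one of three means of determining the effects of the approach. The motive is given earlier in the Background: "there are potential barriers impeding improvement initiatives" and "Another barrier may be the organizational culture of a hospital".

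**The concern.** A barrier to an improvement initiative is something that weakens the response to that initiative. Showing this requires comparing how a characteristic relates to change under the approach with how it relates to change under usual care. The randomised usual-care arm makes that comparison possible, and the determinants models as described do not use it.

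The candidate list is also not one analysable set. A usual-care clinic has no EOV, so it has no EOV score, and the section does not say whether the models cover 32 clinics or 16. A reader of the results could take a characteristic that goes with improvement everywhere as one that makes the approach succeed.

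**Working it through.** The protocol gives no figure for the determinants analysis, so there is none to reproduce. The check sets the stated variables against the two models they allow, and then illustrates the size.

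**1. Which model can be fitted.** Patient, clinic and culture variables: 32 clinics. EOV team variables: 16 clinics, all in one arm.
- *With EOV variables in the model:* usual-care clinics have structurally missing values and drop out. Arm is then constant and no arm term can be estimated.
- *Without EOV variables:* all 32 clinics can enter, but arm is not among the stated candidates.

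**2. What each coefficient estimates.** Let b_I and b_U be the slopes of change on a determinant under intervention and usual care. With 16:16 allocation and the determinant similarly distributed in both arms:
- pooled model: (16/32)·b_I + (16/32)·b_U
- intervention clinics only: b_I
- arm-by-determinant term: b_I − b_U

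Only the third separates response to the approach from ordinary change.

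**3. Error term in the pooled model.** Omitting an arm effect δ raises the residual variance from s² to s² + δ²·(1/2)(1/2). With δ = 0.25 (Sample size calculation), the addition is 0.0625 × 0.25 = 0.0156.
- s = 0.24: √(0.0576 + 0.0156) = 0.271, a ratio of 1.13. Simulated standard errors were 0.050 without arm and 0.045 with it, a ratio of 1.11, because fitting arm costs a little precision.
- s = 0.17: √(0.0289 + 0.0156) = 0.211, a ratio of 1.24.

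**4. Where s comes from.** The SD of clinic-level change is an assumption, because the protocol gives no outcome SD. Solving SD = 0.25 / [(1.960 + 0.842)·√(2/n)] from its 93 couples gives 0.430 if 93 is the total (n = 46.5 per arm) and 0.608 if it is per arm; the text does not say which. With ICC 0.13 and 30 couples per clinic, SD²·(0.13 + 0.87/30) = SD² × 0.159 gives s = 0.171 or 0.242. This is the SD of a clinic mean at one wave. It equals the SD of change if a clinic's two means correlate at 0.5, since 2(1 − 0.5) = 1.

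**5. Illustration.** 4,000 simulated sets of 32 clinic changes, arm effect 0.25, standardised determinant, least squares, two-sided 0.05. Ranges span s = 0.24 to s = 0.17.

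| Slope, usual care / intervention | Pooled, no arm: mean slope; flagged | Intervention clinics only: flagged | Interaction: mean; flagged |
|---|---|---|---|
| 0.15 / 0.15 | 0.15; 81–95% | 59–83% | 0; about 5% |
| 0 / 0.15 | 0.075; 31–42% | 59–84% | 0.15; 37–60% |
| −0.075 / +0.075 | 0; 5–6% | 20–35% | 0.15; 35–60% |

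Row 1: neither available model can tell a general predictor of change from a modifier of the effect. Row 3: in pooled data, a modifier with opposite slopes would usually be lost at the one-by-one screen, if that screen used P < 0.05. Interaction power at other slopes, with s = 0.24, was about 19% for 0.10 and 55–57% for 0.20.

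**The case against.** **The aim is determinants of change.** The abstract, the aims, both subsection headings and the Discussion all word it so, and none promises to show who benefits. This stands. A reader might infer from row 1 that the models would produce false positives 81–95% of the time. The documents do not support that: under the written aim, a factor that drives change in both arms is a determinant, and flagging it is correct detection. The difficulty arises only if results are read as determinants of the approach's success. The umbrella wording of the aims, the barrier motive in the Background and the link drawn between EOV characteristics and carrying out the action plan all invite that reading.

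**The halving assumes a 32-clinic model.** A reader might infer that a true modifier will be estimated at half its size. That holds only if both arms are pooled, which the text never says. In intervention clinics alone, a slope of 0.20 is recovered in full, with 80% power at s = 0.24, against 46% for the pooled model and 55% for the interaction. This stands too. But that model still cannot separate response from ordinary change.

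**Silence is not exclusion.** The list describes baseline characteristics, its verb is open-ended, and a condensed article may leave adjustment terms to a fuller plan. This has some force: the text does not rule arm out. Yet the section fixes a specific procedure, from the 0.6 rule through the one-by-one screen to three final models, and arm has no place in any step. Putting EOV scores in the same candidate set as all-clinic variables is a stated choice, not an omitted detail.

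**The magnitudes are fragile.** SD, between-wave correlation and slopes are assumed, and the simulation does not cover patient-level determinants. This stands, so the figures serve as illustration only.

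**Conclusion.** The point holds in a limited form. Followed as written, the determinants analysis either drops the usual-care clinics or pools both arms without arm. In both cases it identifies predictors of change and cannot show which clinics or patients respond to the multifaceted approach. The pooled version also leaves the intervention effect in the residual variance, and in any characteristic that differs by chance between the 16 and 16 clinics. With an arm effect of 0.25, the standard error is then larger by about 11% at a clinic-change SD of 0.24, and by up to about 24% at 0.17.

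The structural conclusions need no assumed value: they follow from the allocation and from where EOV data can exist. The percentages rest on assumed SDs, slopes and between-wave correlation. The documents do not support saying that the stated aim is contradicted or that the flagged factors would be false. The effectiveness analysis is untouched, since arm is its independent variable. This is a change worth making, not a threat to the main result.

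**What to change.** In the determinants subsection of Data analysis:

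1. For patient, clinic and culture characteristics measured in all 32 clinics, fit the three models in both arms with randomised arm as a covariate. Add arm-by-determinant terms as exploratory analyses, reported with confidence intervals and the association in each arm. Do not let the one-by-one screen on pooled change decide which interactions are examined.
2. Analyse EOV team characteristics in a separate model limited to the 16 intervention clinics, and say so.
3. Describe main effects as predictors of change, not as determinants of the success of the approach.

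The cost is wording and a few extra model terms; arm is already recorded and no new data are needed. The downside is power. With 32 clinics, the interaction tests reach roughly 20–60% for slopes of 0.10 to 0.20 over most of the assumed range, and more only if the largest slope is paired with the smallest SD. A non-significant interaction should therefore not be read as absence of effect modification.

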### The intervention

Clinics randomized for the multifaceted approach will be exposed to this intervention for 1 year. The content of the multifaceted approach is based on previous interviews with Dutch gynecologists, fertility nurses and hospitals’ quality officers about their potential barriers and facilitators for quality improvement, and on previous studies on patient-centered fertility care
[19,37,38]. These studies reported a large variation between clinics and the need for feedback about current performance for the clinicians involved
[18,19]. However, it is shown that audit and feedback alone is not enough; the effectiveness increases if feedback is detailed, offered in high intensity, with professionals’ involvement and as part of a multifaceted intervention
[39-42]. We therefore designed a multifaceted approach consisting of three elements: audit and feedback, educational outreach visits (EOVs), and patient-mediated interventions.

The feedback consists of a personalized paper report with the clinic’s own results, benchmarked and presented in relation to all 32 participating clinics. To identify aspects of care with priority for improvement, quality improvement scores will be calculated per clinic and presented in the feedback report. The higher a quality improvement score (3 – perceived experience score × importance score from the patients’ perspective), the more need there is for improvement
[18]. The clinics receive this report shortly after baseline measurement and 1 month before the EOV will take place. Prior to this visit, the researcher and representative gynecologist will discuss the results from the baseline measurement and define the most important items for EOV.

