#### Clinic characteristics

Potential determinants at the clinic level will be collected by a professionals’ questionnaire during patients’ baseline measurement and by separate data collection during the EOV. The questionnaire will be spread electronically among all healthcare professionals (for example, gynecologists, residents, nurses, laboratory employees, secretaries, and so forth) working at the fertility departments of the 32 participating hospitals. The questionnaire consists of two parts: 12 general questions about clinic characteristics (for example, number of fertility consultations per year, composition of the fertility team, mean age and sex ratio of the fertility team); and six questions from the Organizational Culture Assessment Instrument, a validated questionnaire to examine organizational culture based on the Competing Values Framework
[47-49]. The Competing Values Framework recognizes that no hospital exhibits only one culture, but that multiple cultures and values coexist simultaneously
[50] (that is, clan/family culture, adhocracy culture, market culture, and hierarchy culture). The four culture types relate to each other on a two-by-two matrix with two axes denoting both the flexibility and the orientation of the hospital to the outside world
[47-49,51-53]. In this study the validated Dutch version of the Organizational Culture Assessment Instrument will be used
[54].

Additional possible determinants at the clinic level of a change in patient-centeredness, patients’ QoL and distress levels will be collected during the EOV. According to the literature, these characteristics may influence successful implementation of the action plan – such as, for example, the level of preparation before and the enthusiasm and agreement of the professional team during the EOV
[55]. The researcher will record these team characteristics on a five-point Likert scale.

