## Trial status

Between June 2011 and October 2011, 32 clinics have been found willing to participate in this study. At the time of submission of the manuscript, the execution of the multifaceted approach, aiming at improving patient-centered fertility care in the 16 intervention clinics, has just started.

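### Outreach-visit team scores exist only in the 16 intervention clinics, yet they are pooled as baseline candidates for the determinants models, so any complete-case model that keeps one loses the usual-care arm

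*Protocol article*

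**What the plan says.** Under Data analysis, the section on determinants of change names a single set of independent variables, described as baseline patient and clinic characteristics. It comprises the patient and clinic background variables, four culture variables, "and the team characteristics collected during EOV". The whole set goes through a correlation check (one of a pair is dropped if the coefficient exceeds 0.6) and then a univariate analysis against the before-after differences. After that, "The variables tend to be associated and show enough interclinic variation will be included in three multilevel linear regression models", one for each outcome, and an R² is reported per model.

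Where the visit scores come from is set out elsewhere in the article:

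- Study design: after the baseline measurement, the clinics are "randomly assigned to usual care (16 clinics) or to the multifaceted approach (16 clinics").
- The intervention: "Clinics randomized for the multifaceted approach will be exposed to this intervention for 1 year". Its three elements are "audit and feedback, educational outreach visits (EOVs), and patient-mediated interventions".
- Clinic characteristics: preparation, enthusiasm and agreement of the team are given as examples of what is scored at the visit. "The researcher will record these team characteristics on a five-point Likert scale".
- Trial status: the approach, "in the 16 intervention clinics, has just started".

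**The concern.** A variable measured at an outreach visit has no value in a clinic that has no visit. This is not ordinary missing data, because there is nothing to impute: the event being scored did not take place. Coding usual-care clinics as zero would turn the score partly into a marker of treatment arm. The variable is also not a baseline one, since it is recorded after allocation and in the course of the intervention.

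Finding determinants is a declared aim, and the Discussion expects the results to help improve care. If a visit score enters one outcome's model but not another's, the models rest on 16 and 32 clinics respectively and their R² values are not comparable. A model confined to intervention clinics has no comparison arm. A clinic feature that goes with improvement there may predict uptake of the intervention, or may predict drift that would have occurred anyway. Halving the number of clinics while adding candidates also makes chance selection more likely and inflates the R² that is to be reported.

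**Working it through.** The article gives no sample size, power or candidate count for the determinants analysis, so there is no figure of its own to reproduce.

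**Step 1. Which clinics have which variables.**

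| Variables | When recorded | Clinics with data |
|---|---|---|
| General clinic questions, culture scores | with the baseline measurement | 32 |
| Visit team scores | at the visit, after randomisation | 16 (intervention only) |

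A complete-case model with any variable from the second row uses 32 − 16 = 16 clinics, all from one arm.

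**Step 2. Counting clinic-level candidates.**

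- General questions: the professionals' questionnaire has "12 general questions about clinic characteristics". Assumption: one variable each, so 12.
- Culture: 4, as stated.
- Visit scores: 3 named as examples; the full number is not given.

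Total: 12 + 4 + 3 = 19. Without the visit scores: 12 + 4 = 16.

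- 16-clinic set: 19 candidates, where an intercept and at most 15 clinic-level slopes can be estimated.
- All 32 clinics without visit scores: 16 candidates.

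**Step 3. Chance of a spurious candidate.** With k independent null candidates each tested at 0.05, the chance of at least one significant result per outcome is 1 − 0.95^k.

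- k = 19: 1 − 0.95^19 = 0.62
- k = 16: 1 − 0.95^16 = 0.56

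**Step 4. R² from noise alone.** Simulation with 4,000 runs per setting: independent normal clinic-level candidates, an unrelated normal outcome, the clinic as unit, a univariate screen, then a joint model of whatever passes. The entry level of 0.05 is the significance level the article sets for all analyses. The level of 0.20 is an assumption, shown because the entry rule is worded as a tendency to be associated, with no number and no cap.

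| Clinics | Candidates | Entry level | Mean number kept (maximum) | Mean clinic-level R² |
|---|---|---|---|---|
| 16 | 19 | 0.05 | 1.0 (5) | 0.27 |
| 16 | 19 | 0.20 | 3.8 (10) | 0.52 |
| 32 | 16 | 0.05 | 0.8 (6) | 0.13 |
| 32 | 16 | 0.20 | 3.2 (9) | 0.27 |

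Moving from all 32 clinics without the visit scores to 16 clinics with them roughly doubles the R² that chance alone produces: 0.27/0.13 = 2.1 and 0.52/0.27 = 1.9. No simulated final model held as many variables as clinics.

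**The case against.** The best defence is that this is a wording gap in a secondary aim. The usual-care arm is lost only if a visit score survives screening and the model is complete-case, and a later analysis plan could state the analysis set. The first part is right and limits the claim. The second does not remove it, because the article does not merely leave the set open: it puts the visit scores in the common list, calls that list baseline, and sends it to one model per outcome.

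The figures are also open to challenge. The count of 19 depends on one variable per question and on items given only as examples. The simulation takes candidates as independent, omits the correlation filter and leaves out patient-level determinants. Its R² is at clinic level: at the intracluster correlation of 0.13 used in the sample size section, even 0.52 is only about 0.52 × 0.13 = 0.07 of total variance. All of this stands, so the figures show an order of magnitude and are not forecasts.

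Four stronger readings are tempting, and the article does not support them.

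- A reader might infer a choice between losing the control arm and having more candidates than clinics. These are not alternatives: 19 is below 32, so candidates outnumber clinics only once the control arm has gone.
- A reader might infer that 19 variables are fitted together. They are screened, and the filters leave far fewer.
- A reader might infer that the univariate step ignores clustering, which at 30 patients per clinic and a correlation of 0.13 would give a false-positive rate of 2(1 − Φ(1.96/√4.77)) = 0.37. But univariate may simply mean one predictor at a time. The article does not say which, and the correlation is not given for change scores.
- A reader might infer that the interclinic-variation condition rules out patient-level determinants. That is one reading of an unclear sentence, and the stated aim explicitly includes the patient level.

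**Conclusion.** The point holds. The article pools variables that can exist only after randomisation in 16 of the 32 clinics with variables from all 32, and treats them as baseline candidates for the same three models. Followed as written with complete cases, any model that keeps a visit score describes the intervention arm alone. It then cannot separate determinants of response from determinants of ordinary change, and its R² cannot be set beside that of a model on 32 clinics.

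In the 16-clinic set, about 19 candidates with no numerical entry rule give a mean clinic-level R² of about 0.27 (entry at P<0.05) to 0.52 (entry at an assumed P<0.20) when nothing is real. These values rest on the candidate count in step 2 and on independent candidates. The structural problem in step 1 rests on neither. The effect is confined to the determinants aim.

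**What to change.** In the section on determinants of change:

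1. Remove the visit team scores from the common list and stop describing them as baseline.
2. Fit the three main determinants models on all 32 clinics, with study arm as a covariate.
3. Analyse the visit scores in a separate, explicitly exploratory model of the 16 intervention clinics, with one or two clinic-level variables at a time.
4. Run the univariate screen with the same random clinic intercept as the final models, and give its entry threshold as a number.

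A determinant-by-arm term should not be added for every candidate. By the count above that would make 16 + 16 + 1 = 33 clinic-level terms for 32 clinics and bring the overfitting back.

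The cost is a change of analysis wording and one extra exploratory model; no new data are needed. There are two downsides. The visit scores are no longer mutually adjusted with the other determinants in one model. The main models describe determinants of change with arm held constant, which is what the aim asks for, and not determinants of response to the intervention. Some chance selection also remains with 32 clinics (mean noise R² of 0.13 to 0.27), so the reported R² should be read with that in mind.
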